### Data analysis plan

The intention-to-treat (ITT) population will include all patients randomised to one of the two treatment groups. These groups will be analysed according to the ITT principle (analysed as randomised). The per-protocol (PP) population will only include those patients who underwent the procedure they were randomised to. Statistical analysis will be performed by using SPSS (IBM SPSS Statistics V.25).

#### Primary outcome analysis

Anatomical success at 12 months of follow-up is a dichotomous variable and will be described as numbers with percentages. The difference between the two groups will be presented as a percentage with a 95% CI. If the lower limit of this CI does not exceed the non-inferiority margin of −10%, the intervention will be considered to be non-inferior. A second analysis will be performed in which data from the last follow-up visit before a reintervention will be used in patients undergoing a reintervention of the GSV after failure of primary treatment.

These analyses will be performed for both the ITT and the PP population. Patients with missing data on the primary outcome parameters will be excluded from analyses.

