#### Anatomical success

The calculation is based on the hypothesis that MOCA using Flebogrif will have no inferior anatomical success 12 months after treatment, compared with EVLA. The anatomical success rate in the EVLA group is expected to be 95%.^22^,^25^ The anatomical success rate in the Flebogrif group is expected to be 93%.^18^,^20^ A non-inferiority margin of −10% is applied. This margin is based on the anatomical success rate of 85% after MOCA using Clarivein.^14 25 26^ Taking into account a power of 80% and a significance level of 2.5% (one-sided test on the lower level of the 95% CI of the expected difference), 278 patients will be needed (https://www.sealedenvelope.com/power/binary-noninferior/). Corrected for 10% lost to follow-up, 155 patients need to be included in each treatment group. The total study population will consist of 310 patients.

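### The non-inferiority criterion is worded in reverse: with a signed margin of −10%, the text passes lower limits at or below −10%, contrary to the test used for the sample size

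*Protocol article*

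**What the plan says.** The section Primary outcome analysis describes the comparison of 12-month anatomical success in these terms: "The difference between the two groups will be presented as a percentage with a 95% CI". The decision rule follows: "If the lower limit of this CI does not exceed the non-inferiority margin of −10%, the intervention will be considered to be non-inferior". The section then adds a second analysis, which uses the last visit before a reintervention for patients re-treated after failure of the primary treatment. It closes the paragraph on populations with "These analyses will be performed for both the ITT and the PP population".

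The sample size section (Sample size calculation and drop-out, Anatomical success) gives the margin with the same sign: "A non-inferiority margin of −10% is applied". It expects 95% success with EVLA and 93% with Flebogrif, sets power at 80%, and specifies "a significance level of 2.5% (one-sided test on the lower level of the 95% CI of the expected difference"). The result is 278 patients, raised to 155 per group and 310 in total for 10% loss to follow-up.

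**The concern.** The margin carries a minus sign in both places. On the number line, a value that does not exceed −10 lies at or to the left of −10. The sentence therefore grants non-inferiority when the interval reaches the margin or passes it, and withholds it when the whole interval lies on the acceptable side. That is the opposite of a non-inferiority test and of the test for which the trial was sized.

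This is the only place in the article where the rule for the trial's conclusion is written out. The published criterion should agree with the test that was powered, so that nobody has to infer the rule once the results are known.

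A smaller point lies next to it. The analysis is run in two populations, and a second version handles reinterventions differently. The text does not say whether the ITT result, the PP result or both must meet the margin, nor which handling of re-treated failures decides.

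**Working it through.** **Inputs.** EVLA success 0.95, Flebogrif success 0.93, margin 0.10, one-sided level 0.025 (z = 1.960), power 0.80 (z = 0.842), 10% loss: all from the sample size section. Allocation 1:1: from Randomisation and blinding.

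**Step 1: reproduce the stated sample size under the intended rule (lower limit L > −10 points).**

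n per arm = (1.960 + 0.842)² × (0.95×0.05 + 0.93×0.07) / (0.10 − 0.02)²
= 7.849 × (0.0475 + 0.0651) / 0.0064 = 138.1, rounded up to 139 per arm, or 278 in total.

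With 10% loss: 139 / 0.9 = 154.4, rounded up to 155 per arm, or 310 in total. Both stated figures reproduce exactly.

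**Step 2: expected lower limit at the design rates.**

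SE = √(0.1126 / 139) = 0.0285, i.e. 2.85 points.
L = −2 − 1.96 × 2.85 = −7.6 points.

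This is above −10. It passes the intended rule and fails the literal one.

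**Step 3: chance of declaring non-inferiority, 139 per arm.** For the intended rule, P(L > −10) = Φ((d + 0.10)/SE − 1.96), where d is the true difference. The literal rule gives the complement.

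| True EVLA / Flebogrif | Intended rule (L > −10) | Literal rule (L ≤ −10) |
|---|---|---|
| 95% / 95% | 96.9% | 3.1% |
| 95% / 93% | 80.3% | 19.7% |
| 95% / 85% (at the margin) | 2.5% | 97.5% |
| 95% / 75% | about 0% | about 100% |

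Full binomial enumeration of the Wald interval agrees for the intended rule: 79.6% at 95/93 and 3.1% at 95/85. Only the intended rule gives the stated 80% power and 2.5% level.

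**Step 4: the secondary point.** Primary outcome defines success by occlusion of the treated segment on duplex at 12 months. Reinterventions records re-treatment of failed veins from 1 week onwards. In the first analysis, a vein that failed, was re-treated and is occluded at 12 months could count as a success. The second analysis takes the visit before the re-treatment.

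The documents give no re-treatment rate, so the following is an illustration with assumed values: 0% to 50% of failures in each arm re-treated and then counted as successes, and 2% to 5% of patients outside PP. True primary success is 95% versus 85%, and the corrected rule is applied with 139 per arm.

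- At 50% re-treated, the first analysis compares 97.5% with 92.5%, so the apparent difference is −5 points. SE = √((0.0244 + 0.0694)/139) = 0.0260, and Φ(0.05/0.0260 − 1.96) is about 0.49. Simulation gives 49% to 52%.
- Over the whole assumed range, simulation gives about 3% to 52% for the first analysis and about 3% for the second.
- In each setting, ITT and PP versions of the same analysis differ by less than 3 percentage points. The handling of re-treated failures matters far more than the population.

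**The case against.** The strongest reply is that the intended rule can be recovered. In ordinary speech, not exceeding a margin can mean not going beyond it, and beyond −10 in that sense means below it. The sample size section names a one-sided test on the lower limit, and its figures fit only L > −10. The stated aim is to show that Flebogrif is not inferior. All of this stands: this is an error of wording, not of design.

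Three stronger readings are tempting, and the documents do not support them.

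- A reader might infer that the trial has about 20% power and a 97.5% error rate. Those figures describe only the literal sentence. They would arise only if an analyst ignored the sample size section and declared non-inferiority at, say, −15.
- A reader might infer that the direction of subtraction is open. It is not written down, but a negative margin applied to a lower limit, with Flebogrif expected to be 2 points worse, fits only Flebogrif minus EVLA.
- A reader might infer that the rule is attached to four intervals (two analyses in two populations), any of which could be cited. The rule refers to the interval in the sentence just before it, that of the first analysis, and is not restated for the second. It therefore attaches to two intervals, ITT and PP. The reversal comes from the verb alone and has nothing to do with the number of intervals.

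It is also fair to say that the ranking of ITT and PP is often left to an analysis plan, which is not shown here. That is why it is only a secondary point.

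**Conclusion.** The criterion as printed is wrong and contradicts the sample size section. With a signed margin, it accepts lower limits at or below −10 and rejects those above. Under the design assumptions it would fail the expected lower limit of −7.6 points, while the stated 278 patients and 80% power hold only for L > −10. This rests on the article's own rates, margin and level, with the unpooled normal approximation, checked by enumeration.

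The practical risk is limited, because the intent is plain from the sample size section and a reversed verdict is unlikely. The reason to correct the sentence is that the published decision rule should state the test that will be made.

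Which analysis decides is a separate, lesser matter. The illustration shows that the handling of re-treated failures could matter a good deal, but its size depends on re-treatment rates that the documents do not give.

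**What to change.** Replace the decision sentence with: *Difference = success(Flebogrif) minus success(EVLA), in percentage points. Non-inferiority is concluded if the lower limit of the two-sided 95% CI lies above −10 percentage points.*

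Then add one sentence, in the protocol or the analysis plan and before the 12-month data are analysed, that says whether ITT, PP or both must meet this criterion and how re-treated failures are counted in the deciding analysis. That analysis should not be one in which a re-treated failure can count as a success. Whether to require both populations is a matter of convention. If both are required, the power cost depends on how many patients fall outside PP, which the documents do not give.

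The cost is a wording amendment. The sample size, the margin, the level and the data collection stay as they are.

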### Primary outcome

#### Anatomical success (at 12 months)

Anatomical success (at 12 months) is objectified at 12 months follow-up using DUS. DUS is performed with the patient in the upright position, applying manual compression to the calf and using the Valsalva manoeuvre to detect flow and reflux. Occlusion is defined as a non-compressible vein (segment) that subsequently lacks flow and reflux. Recanalisation is defined as a compressible vein (segment) with flow or reflux.

Anatomical success outcomes (at 12 months) are defined as:

Anatomical success: complete occlusion of the treated vein segment or a recanalised segment of ≤5 cm.Anatomical failure:Partial recanalisation: a recanalised segment of >5 cm.Complete recanalisation: recanalisation of the entire treated vein segment.

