#### Reinterventions

A reintervention is defined as a secondary treatment of the GSV in patients with anatomical failure after Flebogrif or EVLA treatment and assessed at 1 week, 1, 6, 12, 24 and 60 month(s) follow-up.

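### The −10% rule is applied to the 12-month scan with no condition on earlier re-treatment of the GSV, so a failed and re-treated vein can count as a success in the deciding analysis

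*Protocol article*

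**What the plan says.** All references are to the protocol article.

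- **Primary outcome, Anatomical success (at 12 months):** "Anatomical success (at 12 months) is objectified at 12 months follow-up using DUS". Success is complete occlusion, or recanalisation over no more than 5 cm, of the treated segment on that scan. Freedom from re-treatment is not a condition.
- **Secondary outcomes, Reinterventions:** "A reintervention is defined as a secondary treatment of the GSV in patients with anatomical failure after Flebogrif or EVLA treatment". Reinterventions are assessed at 1 week and at 1, 6, 12, 24 and 60 months, so they can occur before the primary scan.
- **Data analysis plan, Primary outcome analysis:** the between-group difference in 12-month success is given with a 95% CI, and its lower limit is compared with −10%. Only after this rule does the text add: "A second analysis will be performed in which data from the last follow-up visit before a reintervention will be used in patients" with a GSV reintervention after failure of the primary treatment. Both analyses are run in ITT and PP.
- **Data analysis plan, populations:** "The per-protocol (PP) population will only include those patients who underwent the procedure they were randomised to". Patients who received their allocated procedure and were re-treated later therefore stay in both populations.

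**The concern.** The Introduction gives the aim as showing that Flebogrif is not inferior to EVLA for anatomical success. A vein that failed, was treated again and is occluded at 12 months says nothing good about the allocated treatment. As written, the analysis that carries the decision rule can nevertheless record it as a success.

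In a non-inferiority trial this matters in one direction above all. The arm with more failures has more patients who can be rescued. With similar re-treatment shares, rescue moves the two observed rates closer together, and a device that is truly worse by the full margin passes more often than the nominal 2.5%. Reporting both ITT and PP gives no protection, because re-treated patients are in both.

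**Working it through.** **Inputs from the protocol article** (Sample size calculation and drop-out): expected success 95% with EVLA and 93% with Flebogrif; "A non-inferiority margin of −10% is applied"; "a power of 80% and a significance level of 2.5% (one-sided test on the lower level of the 95% CI"; 278 evaluable patients, 310 after 10% loss to follow-up.

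**Inputs that are assumptions:** the share f of failures re-treated before the 12-month scan (range 5% to 50%), and 95% of re-treated veins occluded on that scan. The article gives neither.

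**Step 1: the plan's own figure.**
n per arm = (1.960 + 0.842)² × (0.95×0.05 + 0.93×0.07) / (0.10 − 0.02)² = 7.849 × 0.1126 / 0.0064 = 138.1, rounded up to 139, so 278 in total. Then 139 / 0.90 = 154.4, rounded up to 155 per arm, so 310. The stated size reproduces.

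**Step 2: what the first analysis must contain.** The second analysis substitutes the last visit before a reintervention. For the 12-month outcome, that gives a different result from the first analysis only if the first uses the scan made after re-treatment. Together with an outcome defined by the 12-month scan alone, this is the natural reading.

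**Step 3: effect on the observed rates.** With a true success rate p,

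observed success = p + (1 − p) × f × 0.95.

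Put the truth at the margin, 85% versus 95%. Example for f = 25% in both arms:
- Flebogrif: 0.85 + 0.15 × 0.25 × 0.95 = 0.8856
- EVLA: 0.95 + 0.05 × 0.25 × 0.95 = 0.9619
- Observed difference: −7.6 points instead of −10

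In patients, 139 × 0.15 = 20.9 Flebogrif failures and 139 × 0.05 = 7.0 EVLA failures are expected. About 5.0 and 1.7 of them move to success.

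**Step 4: chance of declaring non-inferiority.** For 139 per arm and a Wald interval,

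P = Φ((0.10 + d)/SE − 1.960), where d is the observed difference and SE = √[p_C(1 − p_C)/139 + p_T(1 − p_T)/139] at the observed rates.

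For f = 25%: SE = 0.0315, (0.10 − 0.07625)/0.0315 = 0.754, and Φ(−1.206) = 11.4%. The exact column enumerates all binomial outcomes with the same Wald rule.

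| Share of failures re-treated, both arms | Observed difference | Normal approximation | Exact, Wald rule |
|---|---|---|---|
| 0% | −10.0 | 2.5% | 3.1% |
| 5% | −9.5 | 3.4% | 4.2% |
| 10% | −9.1 | 4.6% | 5.6% |
| 25% | −7.6 | 11.4% | 13.4% |
| 50% | −5.2 | 43.2% | 46.2% |

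**Step 5: unequal rescue.**
- 25% of Flebogrif and 75% of EVLA failures re-treated: 0.8856 versus 0.95 + 0.05 × 0.75 × 0.95 = 0.9856. The difference is −10.0 points and the rate is 2.5% (normal approximation), so the bias cancels.
- 10% versus 50%: 0.8643 versus 0.9738. The difference is −10.95 points and the rate is 1.2%, so the bias reverses.

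**The case against.** **The wording is inferred.** No sentence says that a scan after reintervention counts as success, and both analyses stand under the primary outcome heading. A reader might infer that the protocol expressly designates the post-rescue scan as the deciding result. It does not. What stands is that the rule is stated for the 12-month result before the second analysis is introduced, and that nothing says which result prevails if the two differ.

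**The planners foresaw the problem.** Since reintervention is defined as following anatomical failure, the last visit before it would normally show failure. The second analysis is therefore close to the proposed fix, and a masked failure should show up as disagreement between two planned analyses. This stands and reduces the gap, but it does not close it while the decision rests on the other analysis. A reader might go further and call the second analysis unsafe, because a failure found between visits could leave a success as the last recorded value. The article describes no unscheduled scans and gives no frequency for such cases, so this remains speculation.

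**The direction is conditional.** Re-treatment need not be equal between arms in an open-label trial, and step 5 shows that the bias can cancel or reverse. This stands. It takes a large imbalance, however: three times the share in the EVLA arm to cancel when 25% of Flebogrif failures are re-treated.

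**The size may be small.** At a 5% share the rate is 3.4%. At the planned 95% and 93%, a 25% share means 139 × 0.07 × 0.25 = 2.4 re-treated Flebogrif patients, and the difference moves only from −2.0 to −1.5 points. This is fair, and it is why the low end of the range is shown. The error rate is judged at the margin, where there are more failures to rescue.

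**Same-session conversion.** A reader might extend the point to patients converted to the other technique during the procedure. The article does not mention such conversion, and analysing patients as randomised is ordinary ITT, so the documents do not support that extension.

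**Conclusion.** The concern holds in a limited form. Taking the outcome definition, the reintervention definition and the primary analysis section together, the analysis to which the −10% rule is attached can count a failed and re-treated vein as a success. The analysis that avoids this is planned but is not tied to the rule.

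If failures are re-treated in similar proportions in both arms, the false non-inferiority rate rises from 2.5% (3.1% exact) to between 3.4% (4.2%) at a 5% share and 43.2% (46.2%) at a 50% share. These figures assume a truth of 85% versus 95%, 139 analysed per arm and 95% of re-treated veins occluded. The documents do not give the re-treated share, so this is a range and not an estimate. It would be wrong to conclude that the result is certain to favour Flebogrif, or that the error rate is known to be badly inflated.

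**What to change.** In the primary ITT and PP analyses to which the −10% rule applies, define success as anatomical success on the 12-month DUS with no GSV reintervention before that scan. Any earlier GSV reintervention then counts as failure, whatever a later scan shows. Keep the 12-month scan regardless of reintervention as a sensitivity analysis.

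The cost is an amendment and a matching sentence in the SAP, best settled before 12-month results are compared between arms. Reinterventions are already collected. The size of 278 evaluable and 310 randomised patients does not change if the planning rates of 95% and 93% are rates of primary-treatment success. The downside is that observed success falls slightly in both arms.

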### Study design

The REBORN trial is a two-arm, multicentre, open-label, non-inferiority, observer-blinded, randomised controlled trial. Patients with GSV incompetence referred to the Northwest Clinics Alkmaar, Skin and Vein Clinic Oosterwal Alkmaar and Red Cross Hospital Beverwijk will be screened for eligibility by the vascular surgeon or phlebologist in the outpatient clinic. All eligible patients will receive oral information about the study, an information letter and a participant consent form from the vascular surgeon or phlebologist. After receiving written informed consent, the research coordinator ([name]) performs computer randomisation and informs the patients about the treatment group they are allocated to. The intervention group will receive treatment with MOCA using the Flebogrif device. The control group will receive treatment using EVLA. The procedures will be performed by dedicated vascular surgeons. These vascular surgeons are experienced in performing laser therapy treatment, as this is the current standard treatment for GSV incompetence in our practices. Before treating study participants, all vascular surgeons will undergo training and complete a minimum of five supervised Flebogrif treatments to overcome the initial learning curve.

Patients will be followed up at 1 week, 1, 6, 12, 24 and 60 month(s) after treatment. At each follow-up visit, patients will be seen at the outpatient clinic. A window of 4–14 days will be allowed for 1-week follow-up, 4–6 weeks for 1-month follow-up and ±1 month for 6, 12, 24 and 60 months follow-up. A study flow diagram is shown in figure 1, and table 1 shows all procedures and measurements performed at each follow-up visit.

**Table 1 T1:** Study period, procedures and measurements

	Screening	Intervention	1 week	1 month	6 months	12 months	24 months	60 months
Informed consent	X							
Randomisation	X							
Flebogrif/EVLA		X						
Intraprocedural pain		X						
Operation time		X						
Technical success		X						
Postprocedural pain			X					
Safety				X				
DUS*	X	X	X	X	X	X	X	X
Complications		X	X	X	X	X	X	X
VCSS, CEAP	X		X	X	X	X	X	X
Aesthetic score	X		X	X	X	X	X	X
QoL questionnaire	X		X	X	X	X	X	X

* To assess the outcomes of anatomical success, anterior accessory saphenous vein () reflux and neovascularizsation.

CEAP, Clinical Etiology Anatomy Pathophysiology classification; DUS, duplex ultrasound; EVLA, endovenous laser ablation; QoL, quality of life; VCSS, Venous Clinical Severity Score

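### The 12-month analysis that carries the non-inferiority rule appears to count a failed, re-treated and closed GSV as a success; the analysis that largely corrects this is placed second, with no rule for disagreement

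*Protocol article*

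**What the plan says.** Under the primary outcome, the protocol article states that "Anatomical success (at 12 months) is objectified at 12 months follow-up using DUS". The success category reads "Anatomical success: complete occlusion of the treated vein segment or a recanalised segment of ≤5 cm". Freedom from reintervention is not part of that definition.

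Under Primary outcome analysis, the between-group difference gets a 95% CI, and non-inferiority is judged by its lower limit against −10%. Only after that sentence does the text introduce a second analysis, in which "data from the last follow-up visit before a reintervention will be used in patients undergoing a reintervention of the GSV". It covers re-treated patients "in patients undergoing a reintervention of the GSV after failure of primary treatment". On populations the section adds: "These analyses will be performed for both the ITT and the PP population". It does not say what follows if the first and second analyses lead to different conclusions.

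Under Reinterventions, the article says: "A reintervention is defined as a secondary treatment of the GSV in patients with anatomical failure after Flebogrif or EVLA treatment". The Study design section gives the visits: "Patients will be followed up at 1 week, 1, 6, 12, 24 and 60 month(s) after treatment". Table 1 shows a duplex scan at each of them, so failure can be found and re-treated before month 12.

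**The concern.** A second analysis that substitutes pre-reintervention data for re-treated patients has a purpose only if the first analysis does not do so. The first analysis, which carries the decision rule, is therefore most naturally read as taking the 12-month scan as found. A vein that failed at 1 or 6 months, was treated again and is closed at 12 months then counts in favour of the allocated device. By the article's own definition, a reintervention happens in a patient who already has anatomical failure.

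The aim is to show that Flebogrif is not inferior to EVLA for anatomical success. If Flebogrif fails more often, more of its failures are open to rescue, and scoring rescued veins as successes draws the arms together. In a non-inferiority trial that is the anti-conservative direction. Running ITT and per-protocol analyses side by side does not help. The per-protocol set is defined only by having received the allocated procedure, so rescued veins stay in it as successes.

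**Working it through.** **Inputs from the protocol article (Sample size calculation and drop-out).** EVLA success 95%, Flebogrif success 93%, margin −10 points, one-sided 2.5%, power 80%, 10% loss, 278 evaluable and 310 randomised.

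**Planned figure.** With unpooled variance:

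n per arm = (0.95×0.05 + 0.93×0.07) × (1.960 + 0.842)² / (0.10 − 0.02)² = 138.1, rounded up to 139, so 278 in total.

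139 / 0.9 = 154.4, rounded up to 155 per arm, so 310. Both figures reproduce. Power at 139 per arm is 80.3% by normal approximation.

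**Assumption.** The article gives no reintervention rate. Let r be the share of all failures that are re-treated and found closed at the 12-month scan, equal in both arms.

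**First analysis.** With p the success rate when re-treatment counts as failure:

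observed rate = p + r(1 − p)

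observed difference = (1 − r) × true difference

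The true difference is set at the margin, 95% v 85%. The probability that the lower 95% limit lies above −10% comes from full binomial enumeration at 139 per arm, by Wald and Newcombe intervals, because the article does not name the interval.

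| r | EVLA observed | Flebogrif observed | Difference (points) | P(non-inferior), Wald | P(non-inferior), Newcombe |
|---|---|---|---|---|---|
| 0 | 95.0% | 85.0% | −10.0 | 3.1% | 2.5% |
| 10% | 95.5% | 86.5% | −9.0 | 5.8% | 4.7% |
| 25% | 96.25% | 88.75% | −7.5 | 14.4% | 11.4% |
| 50% | 97.5% | 92.5% | −5.0 | 51.2% | 40.2% |

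The normal approximation gives 2.5%, 4.8%, 12.3% and 48.6% for the same rows.

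**Second analysis.** If every re-treated patient showed failure at the last visit before re-treatment, all are scored as failures. The difference stays at −10.0 points and the error at 2.5% (normal approximation).

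A gap remains where failure was first found between visits and the last visit still showed success. Let u be the share of re-treated patients in that position. The observed rate is then p + r·u·(1 − p). With r = 50%:

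- u = 10%: 95.25% v 85.75%, difference −9.5 points, error 3.5%.
- u = 25%: 95.625% v 86.875%, difference −8.75 points, error 5.6%.

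Both errors are by normal approximation. The remaining bias is small beside that of the first analysis at the same r.

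**The case against.** The first objection is that the problem is inferred. Neither the outcome definition nor the analysis section states that a re-treated, occluded vein is a success. That is so, and the point is put as the most natural reading. But no other reading gives the second analysis a purpose.

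The second objection is stronger. A reader might infer that the last-visit rule refuses to count re-treatment as failure, and that the whole plan is therefore biased towards non-inferiority. The documents do not support this. Reintervention is defined in patients with anatomical failure, and the second analysis is limited to re-treatment after primary failure. The last visit before re-treatment will thus normally show failure, and that analysis largely removes the bias. The 11–14% and 40–51% figures belong to the first analysis only.

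A reader might also see bias towards non-inferiority in the second analysis having no 12-month cut-off, since a reintervention in later follow-up could, read literally, overwrite a valid 12-month result. The effect would tend to run the other way. Replacing 12-month successes with later failures costs most in the arm with more late failures, so it would work against Flebogrif if Flebogrif has more of them. It is a wording gap, not evidence for this concern.

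Finally, r is unknown and may be low. Failures arising after the 6-month visit have no scheduled scan before month 12, and r need not be equal in the two arms. This stands, and is why the table starts at r = 0 and includes 10%. Even at 10%, the error in the first analysis is about double the nominal 2.5%.

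**Conclusion.** The concern holds for the first analysis and for the order of the two analyses. As most naturally read, the analysis carrying the non-inferiority rule credits the allocated device with veins closed by a later treatment. The analysis that mostly avoids this comes second, and no rule settles a disagreement between them.

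In the first analysis, the chance of declaring non-inferiority at a true 95% v 85% rises from 2.5–3.1% with no rescue to 4.7–5.8%, 11–14% and 40–51% when 10%, 25% and 50% of failures are rescued. This rests on equal r in both arms, 139 evaluable patients per arm and an r that the article does not supply, so only the range can be claimed. Because the choice of deciding analysis can change the trial's conclusion, it should be settled before the 12-month data are analysed.

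**What to change.** Under Primary outcome analysis, let the non-inferiority rule apply to this scoring: any GSV reintervention on or before the 12-month duplex scan is anatomical failure; otherwise the 12-month scan decides. Add that reinterventions after that scan do not alter the 12-month endpoint. Keep the as-observed 12-month result, regardless of re-treatment, as a sensitivity analysis. The explicit failure rule also closes the small gap in the last-visit rule when failure is first found between visits.

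The cost is a few sentences. Reinterventions are already assessed at every follow-up visit, so no new data are needed. The 278/310 sample size stands, taking the planned 95% and 93% as success without re-treatment. The change concerns scoring only and leaves patient care as it is.

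The downside is lower reported success in both arms, more so in the arm with more re-treatments. In the table's r = 50% row, Flebogrif would go from 92.5% to 85% and EVLA from 97.5% to 95%; with few re-treatments the change would be slight.
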